　　When incorrect or multiple registrations are found, the registration center should be notified at once.

● Usefulness Evaluation (Phase III)

1. Registration should take place, as a rule, within 14 days of obtaining consent.
2. The principal investigator or assistant investigators will obtain signed consent forms and confirm that participants satisfy the eligibility criteria, and that there is no conflict with the exclusion criteria. Registration forms should be filled in for participants who signed the consent form and sent it to the data center by fax or delivered it in person. The content of the registration forms will be verified at the data center to confirm eligibility. Necessary information for eligible cases will be entered into the system, and all cases will be randomly assigned to either the capnography group or the nasal pressure monitor group at a ratio of 1:1. At the data center, assignment results will be checked and sent to the principal investigator or assistant investigators by fax.
3. Patients who are registered once will not be removed from the database. When the same person is registered multiple times, the initial registration information (Registration No.) should always be used.

When incorrect or multiple registrations are found, the registration center should be notified at once.

* The principal investigator and assistant investigators must not commence the study until registration and assignment of all participants have been completed.

- - 1. **Assignment Adjustment Factors**

Assignment adjustment factors for the usefulness evaluation are procedure (EUS-FNA, ERCP, ESD and DBE), obesity (BMI ≥25, <25), and sex.

- - 1. **Registration Center Location**

Chiba University Hospital Date Center

Business hours: 09:00 – 17:00

Tel; [contact] ([name])

[contact]

- 1. **Handling of Ineligible Patients**

● Safety Evaluation (Phase II)

Patients who are not registered due to ineligibility or other reasons will be counted as non-registered participants and not included as study subjects. Such patients will receive an explanation from the principal investigator or assistant investigators regarding whether or not it is possible to register for the clinical study.

● Usefulness Evaluation (Phase III)

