The screening process will commence after consent has been obtained. The principal investigator or assistant investigators will carry out the following screening tests and select patients who satisfy the eligibility criteria and are not in conflict with the exclusion criteria. Items to check are shown below.

1. Patient background: sex, age, allergies, name of illness to be treated, history of illness, current medication, existing conditions, alcohol consumption, and history of smoking
2. Subjective symptoms
3. Vital signs: heart rate, blood pressure, temperature and SpO_2_
4. Height, weight and neck circumference

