5. ECOG-PS
6. American Society of Anesthesiologists (ASA) Physical Status Classification
7. Sleep apnea-related items (STOP-Bang questionnaire, Mallampati score, and submental soft-tissue excess)
8. 12-lead ECG
9. Chest X-ray
   - 1. **Examination, Testing and Evaluation**
        1. **During Treatment**
10. Sedation start/stop times
11. Subjective and objective findings
12. Vital signs: blood pressure, mean blood pressure and heart rate.

Blood pressure will be taken at 5-minute intervals, other items will be taken at 2.5-minute intervals for 15 minutes after the start of sedation, and at 5-minute intervals thereafter. Measurements will also be taken as required at the discretion of the doctor in charge of sedation. Collect the data for the worst levels (highest or lowest).

1. Monitor (CSM-1901) data
2. Record any ECG monitor abnormalities.
3. SpO_2_: <90% (frequency and duration), <95% (frequency)
4. Apnea (≥20 sec) frequency
5. Respiratory status under SpO_2_ of <90% and <95%
6. False alarm frequency
7. Technical trouble and bodily movement frequency
8. Response to respiratory abnormality

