**Secondary Endpoints for Safety**

Adverse Event Occurrence Rate

NCI-Common Terminology Criteria for Adverse Events v4.0 (CTCAE Ver. 4.0) JCOG version will be used to evaluate adverse events.

Basis for Secondary Endpoint Selection for Usefulness

Items where a difference in occurrence frequency between the capnography group and the nasal pressure monitor group is considered to be important will be evaluated as secondary endpoints.

Basis for Secondary Endpoint Selection for Safety

General evaluation standards will be used.

- 1. **Exploratory Endpoints**
- Comparison with capnography waveforms.
- Waveform analysis at the time of respiratory abnormality.
- Consideration of respiratory abnormality-related risk factors (including obesity, age, history of smoking, drug administration dose, treatment duration, and SAS).

Basis for Exploratory Endpoint Selection

There is a possibility that nasal pressure monitoring can detect the minute changes in waveforms that appear prior to the appearance of a respiratory abnormality. We will compare the changes in the waveforms prior to any drop in SpO_2_ between the capnography group and the nasal pressure monitor group, and analyze to what degree the monitor observer is able to detect changes in waveforms. As there is also a possibility that nasal pressure monitoring can accurately detect the patterns for respiratory depression and obstructive ventilatory impairment, we will analyze the frequency of those events in both groups. We will also consider the relationship between respiratory abnormalities (hypoxemia, apnea and obstructive ventilatory impairment) and obesity, age, drug dose, procedure duration and SAS in order to identify factors relating to respiratory abnormalities.

1. **Statistical Considerations**

The statistical analysis plan overview for the clinical study is shown below. Statistical analysis plan details are contained in the Statistical Analysis Plan. Although the overview of the Study Protocol for the clinical study may be revised in the Statistical Analysis Plan, in cases where the primary endpoint definition or analysis method is to be changed, the Study Protocol will be revised.

- 1. **Analysis Population**
     1. **Full Analysis Set (FAS)**

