**● Usefulness Evaluation (Phase III)**

The purpose of the usefulness evaluation is to prove that there is no difference in the incidence rate of hypoxemia (SpO2 <90%) between nasal pressure monitor group and capnography group, meaning that nasal pressure monitor is not inferior to capnography. According to reports, the incidence rate of declined SpO_2_ to under 90% in the endoscopic procedure under sedation is 12–47% when propofol is used as sedative,[4, 8, 9, 10] With regard to required number of registered patients, calculation based on 20% hypoxemia incidence rate, with non-inferiority margin of 15% for nasal pressure monitor against capnography, statistical power of 80% and significance level of 0.05 on both sides results in 224 patients for both groups (112 patients respectively).

- 1. **Handling Case Records**

In principle, the principal investigator and statistic specialists will decide on how the information on cases will be handled. In principle, the principal investigator and a statistic specialist will decide on how the information on cases will be handled.

- 1. **Handling Data**

When computing or analyzing data, as a rule, the data will be handled as shown below. If a question arises, it will be resolved through discussion between a statistic specialist and the study coordinator.

Missing data will not be supplemented. As sensitivity analysis, mixed-effects model for repeated measures, which compensates for data mission, will be used. Details will be contained in the Statistical Analysis Plan.

- 1. **Statistical Analysis Items and Plan**

● Safety Evaluation (Phase II)

Carry out analysis after the data is fixed following the completion of study involving all cases that are the subjects of safety evaluation. In the usefulness evaluation of all participants, the primary analysis will be the analysis of the FAS, and analysis of the PPS that complies with the Study Protocol will be carried out as a reference. Safety analysis will be carried out with the SAS.

Details of the statistical analysis will be determined in the Statistical Analysis Plan, which will be prepared elsewhere before the data is locked.

● Usefulness Evaluation (Phase III)

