Data from the usefulness evaluation will be analyzed after it is fixed following the completion of the study that involves all cases. In the usefulness evaluation of all participants, the primary analysis will be the analysis of the FAS, and analysis of the PPS that complies with the Study Protocol will be carried out as a reference. Safety analysis will be carried out with the SAS.

Details of the statistical analysis will be determined in the Statistical Analysis Plan, which will be prepared elsewhere before the data is locked.

- - 1. **Patient Background Analysis**

Patient data distribution and summary statistics will be obtained for each group by population. With regard to nominal variables, frequency of the category and proportion will be shown for each group. With regard to metric variables, summary statistics (number of cases, mean value, standard deviation, minimum value, median and maximum value) will be obtained for each group. In the comparison between two groups, Pearson's chi-square test will be used for nominal variables, but if the cells with expected frequency <5 account for 20% or more, Fisher’s exact test will be used. The t-test will be used for metric variables. Significance level will be 0.05 on both sides.

- - 1. **Usefulness Analysis**
       1. **Primary Analysis**

The main purpose of the study is to verify using the incidence rate of hypoxemia as primary endpoint that nasal pressure monitor is not inferior to capnography. Frequency and proportion in each group will be collated and **two-sided 95% confidence interval will be computed** When the upper limit of the 95% confidence interval in the comparison of hypoxemia incidence rate goes 15% lower than the non-inferiority margin, we deem that non-inferiority was proven.

To verify the null hypothesis that incidence rate of hypoxemia in both groups is the same in the primary analysis, Mantel–Haenszel test will be applied to the data stratified using assignment factors. Significance level will be 0.05 on both sides.

- - - 1. **Secondary Analysis**

Secondary analysis regarding usefulness will be carried out for the purpose of giving supplementary consideration to the results of primary analysis. No multiplicity adjustment will be carried out in the secondary endpoints analysis regarding usefulness .

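### The interval that decides non-inferiority makes no stated use of age or STOP-Bang score, both collected at screening; short, prespecified adjustment would be a modest and cheap gain in precision, not the repair of an error

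*Protocol*

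**What the plan says.** **Deciding interval.** Section 11.5.2.1 of the protocol states "Frequency and proportion in each group will be collated", followed by a two-sided 95% confidence interval whose upper limit is compared with the 15% margin. It names no adjusted or stratified estimator for that interval.

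**Stratified test.** The same section adds a Mantel-Haenszel test stratified by the assignment factors. Its null hypothesis is that the two hypoxemia rates are equal. Section 5.4.2 gives the factors as procedure (four types), BMI group (cut at 25) and sex.

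**Baseline data.** Section 7.1.1 collects age with the patient background. It also collects "Sleep apnea-related items (STOP-Bang questionnaire, Mallampati score, and submental soft-tissue excess") and "Vital signs: heart rate, blood pressure, temperature and SpO_2".

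**Stated use of those data.** Section 10.3 has the exploratory item "Consideration of respiratory abnormality-related risk factors (including obesity, age, history of smoking", with drug dose, treatment duration and SAS (sleep apnea syndrome) completing the list. Its rationale counts hypoxemia among the respiratory abnormalities to be examined.

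**Sample size.** Section 11.2 gives a "calculation based on 20% hypoxemia incidence rate, with non-inferiority margin of 15% for nasal pressure monitor against capnography", and "statistical power of 80% and significance level of 0.05 on both sides results in 224 patients for both groups (112 patients respectively").

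**Room for change.** Section 11.5 leaves details to the SAP, which was not available for this review. The opening of section 11 requires a protocol revision if the primary analysis method changes.

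**The concern.** As described, no baseline value enters the interval that settles the trial, not even the factors balanced at assignment. Those factors enter only a test of equality, which cannot establish non-inferiority. Age and STOP-Bang score are not assignment factors, so an interval stratified by those factors would still leave them out.

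If these values predict hypoxemia, adjusting for them removes outcome variance and corrects chance imbalance between the arms. A standardised risk difference stays on the absolute scale, so the 15-point margin and the question are unchanged.

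What is at stake is precision in a trial sized with almost nothing to spare at 80% power. The assumed 20% event rate lies in the lower part of the range the protocol itself cites: the rate "in the endoscopic procedure under sedation is 12–47% when propofol is used as sedative".

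**Working it through.** **Inputs.** From section 11.2: 20% rate in both arms, margin 0.15, power 80%, two-sided 0.05 (one-sided 0.025 for the margin), 112 per arm. From section 5.4.1: patients are "randomly assigned to either the capnography group or the nasal pressure monitor group at a ratio of 1:1". Assumed, because the protocol gives no value: the prognostic strength of the covariates, expressed as R² (share of outcome variance explained) or as the SD of the logistic linear predictor.

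**1. Reproduce the plan's figure.** With unpooled variance, no covariates and no dropout allowance:

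n = 2p(1 − p)(z₀.₉₇₅ + z₀.₈₀)² / δ² = 0.32 × (1.960 + 0.842)² / 0.0225 = 111.63, rounded up to 112 per arm, 224 in total. This matches the protocol.

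SE = √(0.32/112) = 0.0535. Power = Φ(0.15/0.0535 − 1.96) = 80.1%. Interval half-width = 1.96 × 0.0535 = 10.5 points. The unadjusted comparison therefore delivers its stated power.

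**2. Approximate effect of adjustment.** Multiply the variance by (1 − R²), so SE = √(0.32(1 − R²)/112):

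| Assumed R² | Power at 112 per arm | Half-width (points) | Per arm for 80% power |
|---|---|---|---|
| 0 | 80.1% | 10.5 | 112 |
| 0.025 | 81.1% | 10.3 | 109 |
| 0.05 | 82.1% | 10.2 | 107 |
| 0.10 | 84.1% | 9.9 | 101 |
| 0.20 | 88.1% | 9.4 | 90 |

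A simulation with one prognostic score (2,000 trials per setting, standardised logistic risk difference) gave adjusted-to-unadjusted variance ratios of 1.00 at R² 0, 0.98 at 0.025 (AUC 0.61), 0.92 at 0.07 (AUC 0.68), 0.85 at 0.13 (AUC 0.74) and 0.81 at 0.20 (AUC 0.80). The approximation is sound, and nothing material is lost when the covariates predict nothing.

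**3. Other event rates.** At a true rate of 30% in both arms, unadjusted power is 68.8%, or 73.3% with R² 0.10. At 47% it is 61.4%, or 65.9%. Adjustment recovers part of this loss, not all of it.

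**4. How long the model can be.** Expected events are 0.20 × 224 = 44.8, about 45. The assignment factors form 4 × 2 × 2 = 16 cells, on average 224/16 = 14 patients each. A model with arm, the assignment factors, age, STOP-Bang score and room-air SpO2 has 1 + 3 + 1 + 1 + 3 = 9 coefficients plus an intercept. Two models were simulated at 112 per arm (10,000 trials per setting, assignment factors taken as non-prognostic):

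| | Long model, uncorrected influence-function SE | Arm plus two covariates, degrees-of-freedom corrected SE |
|---|---|---|
| Error at the margin (20% vs 35%; unadjusted 2.2-2.6%) | 2.8-3.1% | 2.3-2.7% |
| Behaviour with no prognostic strength | reported SE 0.052, actual SD 0.054 | no material power loss |
| Convergence failure at 20% vs 20% | about 4% of trials | not reported |

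Power of the short model was about 81%, 84% and 85% at linear-predictor SD 0.5, 0.8 and 1.0. Part of the long model's apparent narrowing is a standard error that is too small, and that favours declaring non-inferiority.

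**The case against.** **An unadjusted risk difference is a legitimate primary estimator, and it agrees with the sample size.** This stands. A reader might infer that the trial is underpowered or its decision invalid because covariates are left out. The protocol does not support that: under its own assumptions it has 80.1% power without them.

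**The interval's estimator is open, and the SAP may fill it.** This stands in part. Section 11.5.2.1 never calls the interval crude; that is the natural reading of a description built on group proportions. The SAP could name an interval method. Changing the primary method, however, requires a protocol revision under section 11, so the protocol is the place to settle it.

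**Baseline data are already used.** The Mantel-Haenszel test does use procedure, BMI group and sex, and obesity is among the protocol's own candidate factors. But that test is not the non-inferiority decision.

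**Prognostic value is not established.** A reader might infer that section 10.3 names factors expected to drive hypoxemia. It lists factors to be examined, and their value is the open question. Room-air SpO2 is not on that list, eligibility restricts it to 95% or more, and oxygen is given before sedation. It does not belong in the case.

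**Adjustment can do harm at this size.** This stands for a long model with an uncorrected standard error. It does not stand for two covariates with a corrected one.

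**Conclusion.** The point holds as a missed efficiency gain of modest and uncertain size. The interval that decides non-inferiority is described without baseline information, while age and STOP-Bang score are collected anyway and relate to factors the protocol itself proposes to examine.

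The gain is about zero if these covariates predict nothing, and roughly 1 to 5 points of power (80% to 81-85%) for an assumed linear-predictor SD of 0.5 to 1.0. That range is an assumption; nothing in the protocol fixes prognostic strength. The larger gain, such as 88.1% at R² 0.20, needs stronger prediction than the protocol gives reason to expect. The figures also assume a 20% rate in both arms and 112 analysed patients per arm.

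**What to change.** In section 11.5.2.1, base the deciding two-sided 95% interval on a standardised (g-computation) risk difference from a logistic model, with these elements:

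- Terms: arm, age and STOP-Bang score. Leave out room-air SpO2. Include assignment factors only in a form that sparse levels can support, for example with the rare procedure category merged.
- Standard error: robust, with a small-sample (degrees-of-freedom) correction.
- Timing: covariate list and coding fixed before any Phase III outcome is seen.
- Fallback: report the unadjusted difference and its interval beside the adjusted one, and let it decide if the model fails to converge or shows separation.

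The margin, endpoint and sample size stay as they are. The cost is a protocol revision, matching SAP text and a few lines of code; no new data or patients are needed. The risk is a list that grows: with about 45 expected events, a longer model and an uncorrected standard error bring the error at the margin to about 3%. The short model's figures above are for arm plus two covariates, so if assignment factors are added, repeat the simulation with them before fixing the model.

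### The primary decision rule in section 11.5.2.1 misplaces the 15%: it asks for an upper limit 15% below the margin, whereas section 11.2 makes 15% the margin itself

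*Protocol*

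**What the plan says.** Section 11.2 (Usefulness Evaluation, Phase III) sizes the trial for non-inferiority. It is a "calculation based on 20% hypoxemia incidence rate", "with non-inferiority margin of 15% for nasal pressure monitor against capnography", with 80% power and a two-sided 5% level, and it gives 224 patients, 112 per arm. Section 5.4.1 specifies 1:1 allocation.

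Section 11.5.2.1 (Primary Analysis) repeats the non-inferiority aim, says that a "two-sided 95% confidence interval will be computed", and then gives the decision rule. The rule concerns the upper 95% limit in the comparison of the two rates: when that limit "goes 15% lower than the non-inferiority margin, we deem that non-inferiority was proven". No other criterion for non-inferiority is given.

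The opening of section 11 adds that a change to the primary endpoint definition or its analysis method requires a revision of the protocol itself, not only of the statistical analysis plan.

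**The concern.** In section 11.2 the 15% is the margin. In section 11.5.2.1 the 15% is a distance below the margin. Both cannot describe the same threshold. The words of the rule allow a limit of 0 points (absolute subtraction) or 12.75 points (relative reduction), while the design calls for 15 points.

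The sentence decides whether the confirmatory trial succeeds, so it needs a single threshold. If the observed upper limit fell between 0 and 15 points, the conclusion could depend on which reading was applied. Settling that after the data are known would invite the charge that the threshold was chosen to fit the result.

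**Working it through.** **Inputs**
- Margin 15%, taken as 15 percentage points of absolute difference (section 11.2; this reading reproduces the stated sample size).
- Hypoxemia rate 20%, applied to both arms, so a true difference of 0 (section 11.2).
- Two-sided 5% level, that is 2.5% one-sided, and 80% power (section 11.2).
- 112 per arm (section 11.2), allocated 1:1 (section 5.4.1).
- Two-sided 95% confidence interval (section 11.5.2.1). The protocol names no interval method; a Wald interval is assumed here.

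**Step 1. Reproduce the planned sample size (threshold 15 points)**

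n per arm = [p₁(1−p₁) + p₂(1−p₂)] × (z₀.₉₇₅ + z₀.₈₀)² / margin²

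= 0.32 × (1.960 + 0.842)² / 0.15² = 0.32 × 7.849 / 0.0225 = 111.6, rounded up to 112.

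This matches the protocol. The same formula with 12.75 points gives 111.6 × (15/12.75)² = 154.5, or 155 per arm. With a threshold of 0 and a true difference of 0, no sample size gives 80% power.

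**Step 2. Chance of success at 112 per arm, 20% in both arms**

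Standard error = √(2 × 0.2 × 0.8 / 112) = 0.0535, so the expected half-width of the interval is 1.96 × 0.0535 = 0.105, about 10.5 points.

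Normal approximation: Φ(threshold / 0.0535 − 1.96). The exact column sums over all outcomes of two binomials, using the Wald interval.

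| Reading of the rule | Upper limit must be below | Normal approximation | Exact |
|---|---|---|---|
| Margin is 15% | 15 points | 80.1% | 80.5% |
| 15% relative reduction of the margin | 12.75 points | 66.5% | 66.8% |
| 15 points subtracted from the margin | 0 points | 2.5% | 2.6% |

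Only the first row agrees with the stated 80%.

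**Step 3. How far the last row depends on the assumed rates**

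With equal rates of 12%, 30% or 47% (section 11.2 cites reports of 12–47%), the chance of an upper limit below 0 remains about 2.6%. It rises if the new monitor is truly better. With capnography at 20%, it is 16.7% for a true nasal pressure rate of 15%, and 56.8% for a true rate of 10%.

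**Step 4. An illustration**

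With 22 of 112 patients hypoxemic in each arm (19.6%), the upper limit is 0 + 1.96 × √(2 × 0.196 × 0.804 / 112) = +10.4 points. That result is below 15 and below 12.75 but not below 0. With 12 nasal pressure events against 22, the difference is −8.9 points and the upper limit is +0.4 points, still not below 0.

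**The case against.** The strongest reply is that the intended rule can be recovered from the protocol. Section 11.2 fixes the margin, the Study Outline and section 11.5.2.1 both state a non-inferiority aim, and 112 per arm follows only from a threshold of 15 points. The English is rough elsewhere, and moving one phrase (lower than the margin of 15%) gives a correct rule. Applying the 15-point margin would follow the prospective design and would not loosen it. This largely stands as to intent. It does not make the written sentence correct, and the protocol's own provision in section 11 is that a change to the primary analysis method is made in the protocol.

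A reader might also infer that the protocol prescribes a superiority test with under 3% power. The documents do not support that. Superiority is the most direct literal reading but not the only one, since the relative reading gives 12.75 points. The 2.6% is essentially the one-sided error rate of any superiority test when the true rates are equal; it would be much the same at other sample sizes, and Step 3 shows how it moves when the rates differ. The trial was not designed on that rule.

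Nor is it a strong complaint that the interval belongs to each arm separately or that the direction is missing. The preceding sentence does collate figures by group, but the rule refers to the interval in the comparison. Section 11.2 sets the margin for the new monitor against capnography, and an upper limit on a harmful outcome implies nasal pressure minus capnography. Spelling this out is worthwhile when the sentence is rewritten, but it is not a separate error.

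**Conclusion.** The primary decision rule is misstated and conflicts with the margin in section 11.2. Under the design assumption of 20% in both arms with 112 per arm, the literal readings give a 2.6% or 67% chance of success, against 80.5% for the rule on which the trial was sized. These figures assume an absolute margin and a Wald interval.

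The defect is confined to one sentence and is probably a word-order slip; the sample size is sound and reproduces. It still needs correcting, because that sentence governs the trial's primary conclusion and can currently be read with three different thresholds.

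**What to change.** Replace the decision sentence in section 11.5.2.1, by protocol amendment before data lock, with:

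> Non-inferiority is concluded if the upper limit of the two-sided 95% confidence interval for the difference in hypoxemia incidence (nasal pressure minus capnography) is below the non-inferiority margin of 15 percentage points.

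The statistical analysis plan should carry the same sentence. The cost is one sentence and the review-board approval that section 13.1 requires for a revised protocol. Sample size, procedures and data collection are unchanged.

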This particular clinical study will be conducted to verify that there is no difference in the frequency of hypoxemia between the nasal pressure monitor group and the capnography group. SpO_2_<90% will be used as the general index for hypoxemia.

- 1. **Secondary Endpoints**

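### The Phase III primary analysis adds an unranked test of equal hypoxemia rates, which is not the null of a non-inferiority trial and invites a non-significant result to be read as support

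*Protocol*

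**What the plan says.** Section 11.5.2.1 of the Protocol (Primary Analysis) contains two procedures.

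- **Interval rule.** Hypoxemia rates are compared with a two-sided 95% confidence interval, and non-inferiority is declared from its upper limit and the 15% margin. The method of computing the interval is not named.
- **Equality test.** "To verify the null hypothesis that incidence rate of hypoxemia in both groups is the same in the primary analysis", a Mantel–Haenszel test stratified by the assignment factors is applied at two-sided 0.05. The text gives it no order relative to the interval, no role in the conclusion and no interpretation.

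The assignment factors (section 5.4.2) are procedure in four classes, BMI in two and sex.

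The aim is worded in the same direction as the equality test. Section 10.1 says that the study is "conducted to verify that there is no difference in the frequency of hypoxemia" between the groups. Section 11.2 says that the purpose is to "prove that there is no difference in the incidence rate of hypoxemia", and then explains this as meaning that the nasal pressure monitor is not inferior.

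The sample size in section 11.2 is a "calculation based on 20% hypoxemia incidence rate", "with non-inferiority margin of 15% for nasal pressure monitor against capnography", with "statistical power of 80% and significance level of 0.05 on both sides results in 224 patients for both groups (112 patients respectively").

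**The concern.** In this trial the null to be rejected is that the nasal pressure monitor raises the hypoxemia rate by 15 points or more. Equal rates is the null of a superiority test. A test can reject that null but cannot verify it. Non-rejection becomes more likely as the data become noisier, which is the wrong incentive in a trial meant to exclude harm.

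Placed under the primary heading, without a rank, in a document that describes success as no difference, the test gives a report writer an apparent second route to a favourable statement. What is at stake is the main conclusion about an unapproved respiratory monitor: a trial that did not exclude a 15-point excess of hypoxemia could be summarised as having found no difference.

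A second, smaller matter is that the stratification by assignment factors is written for the test that should not decide the trial, and none is stated for the interval that does.

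**Working it through.** **Inputs.** From section 11.2: 20% hypoxemia (taken for both arms), margin 15 points, "statistical power of 80% and significance level of 0.05 on both sides", 112 per arm, and a literature range of "12–47% when propofol is used as sedative". From section 5.4.2: 4 × 2 × 2 = 16 strata. The documents give no stratum sizes, so the calculation treats the data as one stratum. The sentence stating the interval rule is awkward; it is taken in its evident sense, upper limit below +15 points.

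**Step 1. The plan's own sample size.** With p = 0.20 in both arms and one-sided 0.025:

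n = 2p(1 − p)(1.960 + 0.842)² / 0.15² = 0.32 × 7.849 / 0.0225 = 111.6, so 112 per arm and 224 in total.

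This matches. The design was therefore sized on the margin-based null. A superiority calculation for 20% v 35% would have given 138 per arm.

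**Step 2. Formulas.** With observed rates c (capnography) and t (nasal pressure), n = 112:

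- Interval: U = (t − c) + 1.96 × √[(c(1 − c) + t(1 − t))/n]; non-inferiority is shown if U < 0.15.
- Equality: z = (t − c)/√[2m(1 − m)/n] × √(223/224), where m = (c + t)/2; significant if |z| > 1.96. This is the Mantel–Haenszel statistic for one stratum, without continuity correction.

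**Step 3. Example results.** Capnography has 22/112 events (19.6%).

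| Nasal pressure events | Difference (points) | Upper limit (points) | Equality p |
|---|---|---|---|
| 26 | +3.6 | 14.3 | 0.52 |
| 27 | +4.5 | 15.3 | 0.42 |
| 30 | +7.1 | 18.2 | 0.21 |
| 34 | +10.7 | 22.0 | 0.065 |
| 35 | +11.6 | 22.9 | 0.047 |

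For 27 events: t = 0.2411, c = 0.1964, standard error = √[(0.1578 + 0.1830)/112] = 0.0552, so U = 0.0446 + 1.96 × 0.0552 = 0.153. From 27 to 34 events non-inferiority is not shown and the equality test is non-significant.

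**Step 4. How often this happens.** Exact enumeration over two independent binomials with 112 per arm:

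| True rates (capnography v nasal pressure) | Non-inferiority shown | Not shown, equality non-significant | Not shown, equality significant |
|---|---|---|---|
| 20% v 20% | 80.5% | 17.1% | 2.5% |
| 20% v 25% | 43.9% | 41.8% | 14.2% |
| 20% v 30% | 13.9% | 45.1% | 41.0% |
| 20% v 35% | 2.5% | 25.9% | 71.6% |

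At the two ends of the cited literature range, the middle outcome has probability 4.7% (12%) and 34.3% (47%) with equal rates, and 15.3% and 35.0% with a true difference of 15 points.

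**Step 5. The cost of the misreading.** At 20% v 35%, where the true difference equals the margin, the equality test is non-significant in 2.5% + 25.9% = 28.4% of trials. The interval rule wrongly declares non-inferiority in 2.5%. The ratio is 28.4/2.5, about 11.

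**The case against.** A reader might infer that the protocol has two competing primary criteria that can give opposite answers with no rule for which governs. The text does not support that. Only the interval rule is tied to declaring non-inferiority; no sentence makes a non-significant equality test a success. Section 11.2 explains its no-difference wording as meaning not inferior, and the sample size rests on the correct null. Section 10.1 lacks that explanation, but it gives the reason for choosing the endpoint and is not a decision rule.

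Nor are the 17%, 42% and 45% contradictions. An interval that crosses the margin together with a non-significant equality test is the ordinary inconclusive result, and both statements are true at once. A real contradiction would be non-inferiority shown with the nasal pressure monitor significantly worse. On the same enumeration its probability is about 2 in 100 million at 20% v 20% and below 0.1% at 12% v 12%.

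The 28% describes a rule that the protocol does not contain. Under the rule it does contain, the error at the margin is 2.5%.

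Finally, one might infer that the interval is unstratified. The protocol leaves its method unstated, and the analysis plan, not shown here, may supply it.

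All of this stands, and it limits the point. It does not remove it: the equality null is written into the primary analysis, as something to be verified, with no role assigned. That is a misstatement in the protocol and not a detail left for later. The opening of section 11 requires a protocol revision when the primary analysis method changes, so the analysis plan alone cannot correct it.

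**Conclusion.** The point holds in a limited form. The criterion for declaring non-inferiority and the sample size are sound in design. The defect is a second test with the wrong null, placed unranked in the primary analysis and surrounded by wording that makes non-significance look like the goal.

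The situation in which this could mislead is common at the planned size: 17% of trials with no true difference, and 42% to 45% with a true excess of 5 to 10 points. Misuse would raise the error at the margin from 2.5% to 28%, but that misuse is invited, not prescribed.

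The figures assume 20% hypoxemia under capnography, 112 analysed per arm, a Wald limit and a single stratum. Stratification or another interval method would shift them somewhat. The remark on stratification is that it is stated for the test and not for the deciding interval; no loss of precision was quantified.

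**What to change.** 1. In section 11.5.2.1, state the null as a risk difference (nasal pressure minus capnography) of 15 percentage points or more. Make the two-sided 95% confidence interval for that difference the sole primary criterion, with success if its upper limit is below +15 points.
2. Compute that interval stratified by the assignment factors, for example as a Mantel–Haenszel risk difference, with a rule fixed in advance for pooling sparse cells among the 16.
3. Remove the equality test from the primary analysis, or label it as a superiority test done only after non-inferiority is met. In that fixed order no adjustment of the significance level is needed.
4. In sections 10.1 and 11.2, replace the no-difference wording with: not worse by 15 percentage points or more.

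The cost is a protocol revision and matching wording in the analysis plan. The sample size stays at 112 per arm because it already derives from the margin-based null. The small downside is that sparse strata, possibly those for DBE, may need pooling.
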